### Fatigue Assessment

Fatigue induction studies evaluate real-time changes in fatigue symptoms by self-reporting, performance, and eye tracking. An adapted version of the Visual Analog Scale–Fatigue (VAS-F) [97] will be used as a state fatigue measure given its history of use in fatigue induction research. [27,98,99] A closely linked concept to CF is cognitive workload. Cognitive workload applies an ergonomic and human factors model (eg, elements of a job or task that create a feeling of mental work) to understand fatigue as it relates to sustained work performance [100-104]. The NASA-TLX is a commonly used measure of workload [105,106]. In addition to subjective measures, there are two approaches to use performance data to objectively measure fatigue: change in performance on the induction task or using a pre- versus postintervention cognitive assessment [26,29,107,108]. Tests of reaction time [42], working memory [23], and inhibitory control [32] are used to assess fatigue effects.

Psychophysiological measures identify objective brain or autonomic nervous system indicators of fatigue using EEG (electroencephalogram) [22,23,30,109], ERP (event related potential) [28,31,86,110], functional brain imaging [27,40,107,108], and ECG (electrocardiogram) [29,30] to measure changes in brain or cardiovascular activity associated with fatigue. Of the various physiological indicators, eye tracking has emerged as a promising, noninvasive tool for identifying objective measures of CF. Eye tracking studies show changes in blink rate, percent eye closure, gaze fixation (eg, length and location), and gaze shift rate are associated with CF [30,49-51,111-114]. Changes in gaze shift rate may indicate use of less efficient lower-level cognitive processing [49] and a centralized fixation can indicate a loss of full attention to the task [115]. Several sources, using different task demands, show changes in visual activity as the time on task increases.

### Engineering and Technology

The virtual environment was created using Unity 3D (Unity Technologies). Products will be created by the graphics design team using digital image files obtained from the product manufacturer, labels scanned from acquired grocery items, or modified from items purchased through the Unity Asset Store. All labels are converted into 3D objects using a variety of programs and techniques. The design team will develop a cohesive store branding and coordinated color scheme for store assets. Within the environment, near objects will be displayed with a high degree of visual detail, whereas distant objects will have reduced detail. General product labeling will be legible without selecting the object; however, specific product information (eg, reduced sodium or nutritional values) will only be legible after product selection.

The VIVE Pro Eye (HTC Corporation) will be the HMD device used in each study. This device has a 2880 × 1600-pixel display resolution and includes eye tracking and high-resolution surround sound and allows for the use of glasses and adjustable optics that are designed to minimize eye fatigue and cybersickness. Participants will interact with the virtual environment and objects within the environment by using a wand. The VR program is delivered to the HMD via a display port from a Dell Precision workstation 7920. The technical features of the 7290 include Intel Xeon Gold 5122 3.6 GHz, 3.7 GHz Turbo, 4C, 10.4 2UPI, 16.5 MB Cache, NVIDIA Quadro P5000, 16 GB, 4 DP, and 32 GB 2 × 16 GB DDR4 2666 MHz RDIMM ECC (error correction code) memory. This equipment will have adequate processing power, graphical speed and resolution, and memory to provide a vivid, smooth immersive experience. Eye-tracking data will be collected from individual participants using the integrated eye-tracking system contained within the HTC Vive Pro HMD. The data sampled by the HMD eye tracker include data output (eye information): timestamp (device and system), gaze origin, gaze direction, pupil position, pupil size, and eye openness, which are captured every 200 ms.

### Participants

The participants will be recruited from a local metro region. We anticipate that participant background characteristics (eg, education, ethnicity, sex, and age) will be representative of the metro area in background characteristics (eg, education, ethnicity, sex, and age). Recruitment will be managed by the National Institutes of Health (NIH) Office of Patient Recruitment, using local flyers; Office of Patient Recruitment website; and posts on social media, including Facebook and Twitter. Participants will be remunerated to participate in the study. All protocol activities will take place in a local NIH facility in Bethesda, Maryland. 

For each phase of the study, participants will be healthy individuals aged 18-75 years. Recruitment for phase 1 will target an older (≥55 years) and younger group (18-54 years) with 50% targeted for each group, stratified by sex. Recruiting a broad age range will ensure usability among older individuals, as future apps will likely involve older adult clinical populations. The sample will be stratified by sex, as some research suggests that women may experience immersive VR differently from men [116,117]. The phase 1 sample size will be 24, with 8 participants completing each of the three shopping conditions. Evaluating participants from a variety of backgrounds is important in UX research to identify any systematic issues in the interface, content, or instructions. The phase 2 study recruited 60 healthy individuals aged 18-75 years. For this study, there will be no targeted recruitment of older adults, as any design issues specifically associated with subject age will be addressed before phase 2. The sample size was determined based on the calculated effect sizes of fatigue induction studies that used the VAS-F (Cohen *d*=0.65; SD 0.25) and vigilance decrement studies [34]. The inclusion and exclusion criteria are included in Textbox 1.

Inclusion and exclusion criteria.
**Inclusion criteria**
Participants aged 18-75 yearsWillingness to complete the study procedureWilling to provide feedback on virtual reality experienceAble to provide consent
**Exclusion criteria**
Self-reportedAny impairment in visual functioning (eg, 3D depth perception, color blindness, visual acuity, and oculomotor control) not corrected with lensesEye pain or iritisSusceptibility to photosensitive seizures or diagnosis of seizure disorderInability to use handsDiagnosis of neurological conditionsDiagnosis of sleep disordersCurrent treatment for chronic physical pain, migraines, any diagnosis of a clinical condition associated with cognitive or physical fatigue (eg, multiple sclerosis and chronic fatigue syndrome)History of acquired brain injuriesCurrent cold or flu symptomsNational Institute of Nursing Research employees and staff or subordinates, relatives, and coworkers of National Institute of Nursing Research employees and staff or a study investigatorNot fluent in EnglishFor phase 2, participation in phase 1

### Analysis

#### Overview

This statistical analysis plan was reviewed by the National Institute of Nursing Research (NINR) statistician. All data will be processed, cleaned, and analyzed using the SAS 9.4 (SAS Institute). The data analysis approach for phase 1 focuses on descriptive and nonparametric tests. The primary goal of the phase 1 study is to evaluate the measures and identify any interface issues that cause participants to have problems interacting with the environment or producing unexpected physical symptoms. The phase 2 study will test specific hypotheses using inferential statistics.

#### Phase 1

The data analysis for phase 1 will inform decisions related to programming, data outputs, adequacy of obtained score distributions, evaluation of the psychometric quality of the cognitive tests, and identification of any potential confounds (eg, length of VR exposure) that could impact future studies. We will examine the initial evidence for the fatigue induction effects of the three shopping conditions. We will use frequency and nonparametric procedures to evaluate the rates of observed difficulties using controllers, interacting with the environment, and following instructions generally, by age groups and by sex. We will compare self-reported feelings of distress before entering the VR environment to the self-reported symptoms after exiting the VR environment. For this analysis, the Wilcoxon signed-rank test will be used. Secondary analyses evaluate distributions of key dependent measures including self-reported CF and workload, eye-tracking data (eg, blink rate, percent eye closure, gaze fixation length, and gaze shifts), and performance data for shopping and cognitive tasks (eg, correct response and response speed), as having a score distribution of several SDs will be important when the measures are applied in hypothesis testing. Following a structured interview, responses will be analyzed for common interface or immersive content issues (eg, difficulty teleporting, difficulty reading text, and problems accessing grocery list).

For example, in phase 1, we will compare the participants’ self-reported physical symptoms and eye-related symptoms from the VRSQ before versus after completing the VR shopping experience. We will use the Wilcoxon signed-rank test, given the high probability of a nonnormal distribution in the dependent measure. This comparison will provide evidence to determine whether the VR environment produces physical distress or eyestrain. We computed the total scores for each of the observation scales. These totals inform about the number of times the participant had difficulties with the interface. We will compare the frequencies of interface problems in older and younger and male and female subjects using the chi-square test. These are structured statistical analyses planned as part of the formal UX results. Exploratory procedures are used to identify the relationship between user behavior (eg, number of items reviewed, distance traveled in the environment, and accuracy of shopping behaviors with measures of shopping enjoyment, shopping experience, and sense of immersion in the environment). For these analyses, we used Spearman rank-order correlations.

#### Phase 2

We will use the repeated measures analysis of variance (ANOVA) with the VAS-F and NASA-TLX as repeated dependent variables by shopping experience (fixed) to test the hypothesis that grocery shopping creates fatigue and workload, particularly when the person experiences interruptions and distractions. Secondary analyses will evaluate whether objective indicators of fatigue, such as eye tracking, shopping performance, and cognitive functioning (eg, pre- and postshopping processing speed and working memory) significantly differ by shopping experience using repeated measures ANOVA. A third series of analyses evaluated the relationship among individual characteristics, perceived CF, and workload. We will primarily use correlation to evaluate the relationship among pre-existing symptoms of fatigue, anxiety depression, personality traits, and fatigue susceptibility. Cognitive measures from the NIH toolbox will be correlated with perceived fatigue and workload to identify whether cognitive abilities influence the perception of cognitive workload and fatigue.

For example, we will use the repeated measures ANOVA to test the primary hypothesis that the cognitive activity of shopping for specific items will create a greater perception of mental workload and fatigue compared with just exploring the environment unless the distribution of dependent measures does not allow for using this specific statistical procedure. Similarly, we will use an appropriate correlation procedure to compare the level of activity measures such as distance traversed in the store, number of items selected and reviewed, and efficiency and accuracy of shopping activity with perceptions of fatigue and workload. Correlation procedures will be used to assess the relationships between constructs, such as personality style, cognitive ability, fatigue susceptibility with self-reported mental workload, and fatigue to identify individual differences in fatigue susceptibility. Eye tracking such as percent eye closure will be explored as a possible objective indicator of fatigue by serving as a dependent measure in the repeated measures ANOVA by shopping experience and in correlational analysis with self-reported fatigue and workload. The actual analysis considers the appropriateness for each specific variable distribution.

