The aim of phase 1 is to evaluate the design elements of the virtual shopping environment to identify any factors that may hinder the ability of participants to effectively perform tasks in the virtual environment, identify the risk of physical distress, and obtain user feedback about realism and functionality. The primary hypothesis for the UX study is that the VR environment will be acceptable; however, some users will exhibit minor difficulties using the controllers and interacting with the environment. The primary outcome measures will be observational ratings assessing user difficulties with controller use, interacting with objects, and moving in the environment. The secondary hypotheses include that participants will report only minimal feelings of distress, will report that the virtual grocery store appears realistic and immersive, and will provide a general positive response to the experience with additional helpful ideas about how the experience could be improved.

The primary aim of phase 2 is to evaluate individual and environmental characteristics associated with susceptibility to experiencing CF in the context of performing an IADL, specifically shopping. Our primary hypothesis in phase 2 is that individuals performing structured grocery tasks will report more CF than simple exploratory behavior in the grocery store and that individuals experiencing distractions and interruptions will report more fatigue than those who do not experience interruptions. The primary outcome measure in phase 2 is the self-reported change by participants in CF by shopping experience. The secondary aims of phase 2 are to identify performance and eye-tracking measures that objectively identify fatigue, cognitive abilities, personality characteristics, shopping experience, or transient mood states that affect susceptibility to fatigue during shopping. Specific secondary exploratory hypotheses include that perceived workload increases with time on task for structured tasks and disruptive environments, percent eye closure and gaze shift increase with time on task and are associated with self-reported fatigue, and shopping accuracy declines with time on task.

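### The phase 1 comparison of interface difficulties by age and sex uses a chi-square test with no stated unit; on pooled event counts it would ignore repeated events within a participant

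*Protocol article*

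**What the plan says.** The Objectives section of the protocol article sets the phase 1 primary outcome: "The primary outcome measures will be observational ratings assessing user difficulties with controller use, interacting with objects, and moving in the environment". Under Methods, Analysis, Phase 1, total scores are computed for each observation scale, and the article explains: "These totals inform about the number of times the participant had difficulties with the interface". The variable is therefore a count per person, and one person can contribute several events.

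The next sentence names the test: "We will compare the frequencies of interface problems in older and younger and male and female subjects using the chi-square test". The one after it gives the status of these analyses: "These are structured statistical analyses planned as part of the formal UX results". Earlier in the same section the approach is put more generally: "We will use frequency and nonparametric procedures to evaluate the rates of observed difficulties using controllers", by age group and by sex.

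On numbers, Methods, Participants states: "The phase 1 sample size will be 24, with 8 participants completing each of the three shopping conditions". For the groups being compared it says: "Recruitment for phase 1 will target an older (≥55 years) and younger group (18-54 years) with 50% targeted for each group, stratified by sex". That gives 12 older and 12 younger participants. No sex ratio is stated.

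**The concern.** Pearson's chi-square test requires independent units. Two difficulties recorded in the same participant are not independent if participants differ in how readily they get into difficulty. The Objectives section expects that only some users will have minor difficulties, so events should cluster in a minority. The three shopping experiences also place quite different demands on the user, which may add to the spread between people.

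The sentence naming the test follows directly on the one describing per-participant totals, so pooling the events in each group is a natural way to carry it out. A few struggling users in one group could then produce a significant age or sex difference that reflects those individuals only.

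Phase 1 data are meant to improve the interface before phase 2 (Methods, Study Design) and to inform programming decisions (Methods, Analysis, Phase 1). A misleading subgroup difference would be part of that evidence.

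**Working it through.** **Plan's own figure.** The article gives no alpha, expected count or dispersion for this comparison, so there is nothing to reproduce. The sample sizes agree: 3 × 8 = 24, and 24 + 60 = 84.

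**Inputs from the article.** 24 participants; 50% in each age group, so 12 versus 12; outcome a count per participant.

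**Assumed inputs.** Two-sided alpha 0.05; about 12 versus 12 by sex; the mean count per person; and VMR, the between-person variance-to-mean ratio of the counts.

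**Reading 1: events pooled.** Let A and B be the total events in the two groups of 12. The chi-square statistic for equal expected totals is (A − B)²/(A + B), compared with 3.84. With no true difference and mean count μ per person:

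- Var(A − B) = 24 × μ × VMR
- E(A + B) = 24 × μ
- so the statistic behaves approximately as VMR times a chi-square variable on 1 df
- actual type I error ≈ 2 × (1 − Φ(1.96/√VMR))

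| VMR | 1.96/√VMR | Type I error |
|---|---|---|
| 1 | 1.960 | 0.05 |
| 1.5 | 1.600 | 0.11 |
| 2 | 1.386 | 0.17 |
| 3 | 1.132 | 0.26 |
| 5 | 0.877 | 0.38 |

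The formula was checked by simulation: 20,000 replicates per scenario, Poisson or negative binomial counts, means from 1 to 10 per person. The two agreed to within about 0.01. Simulated values were, for example, 0.110 at VMR 1.5, 0.164 to 0.169 at VMR 2 and 0.255 at VMR 3.

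A second model gave each person a fixed number of opportunities, an event probability of 0.2 and an intraclass correlation of 0.05 to 0.3. Type I error was 0.07 to 0.19 with 5 opportunities, 0.11 to 0.32 with 10, and 0.16 to 0.46 with 20. With zero correlation it stayed at 0.05.

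**Reading 2: participants with any versus no problem.** The units are now independent. Simulated type I error ranged from 0.000 to 0.065, and was lowest when nearly everyone had a problem. With k of 24 participants affected and 12 per group, the expected cells are k/2 and (24 − k)/2. One of these is below 5 when k < 10 or when 24 − k < 10, that is, when fewer than 10 or more than 14 participants have the problem.

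**Alternative: rank-sum test on per-participant totals.** In the same count scenarios (4,000 replicates each), type I error was 0.038 to 0.051.

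**The case against.** The strongest reply is that the article never says events are pooled. Frequencies of problems among subjects can also mean the number of subjects showing a problem, and the general statement about nonparametric procedures leaves room for rank methods. This stands. A reader might infer that the plan certainly inflates false positives, but the text does not fix the unit, and on the participant reading the error is not materially inflated.

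The size of the inflation also rests on dispersion values that the article does not supply. If all participants shared one Poisson rate there would be none. That stands too, although the article's expectation that only some users will struggle makes a ratio of exactly 1 unlikely.

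A reader might further infer that this test decides whether the interface is redesigned, or that it is the stated reason for not targeting older adults in phase 2. Neither is supported. Phase 1 decisions also draw on interviews and symptom scores, and no rule is tied to this p-value. The reason given in Methods, Participants is that age-related design issues will have been dealt with before phase 2; this test is not mentioned there.

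Finally, phase 1 is largely descriptive, and its primary hypothesis concerns acceptability, not an age or sex difference. That limits the weight of the point. It does not remove it, because the article names the test and counts it among the formal results.

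**Conclusion.** The point holds as an undefined unit of analysis joined to a test that suits neither reading well. If events are pooled, independence fails, and type I error runs from 0.05 at VMR 1 to about 0.38 at VMR 5, with alpha and the VMR values assumed. If participants are classed as any versus no problem, false positives are not the issue: the comparison discards the counts the article has just described, becomes very conservative when nearly everyone has a problem, and often has expected cells below 5. The 12 versus 12 split is stated for age and assumed for sex.

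The consequence is a possibly misleading age or sex finding among the data that inform interface changes. The phase 2 primary test is not affected. The change is worth making because a rank-sum test on the totals keeps the participant as the unit, uses the counts, and fits the rank methods the same section already chooses for the symptom scores and the exploratory correlations.

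**What to change.** Replace the chi-square sentence in Methods, Analysis, Phase 1 with wording that makes the participant the unit. For example: total difficulties per participant will be compared between age groups and between sexes with the Wilcoxon rank-sum test; where a yes/no difficulty variable is wanted, it will be defined per participant and compared with Fisher's exact test; pooled event counts will not be tested with chi-square.

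The cost is one sentence. The totals are already planned, so no new data or participants are needed.

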**Methods:**

We will recruit 84 healthy participants (aged 18-75 years) for a 2-phase study. Phase 1 is a user experience study for testing the software functionality, user interface, and realism of the virtual shopping environment. Phase 2 uses a 3-arm randomized controlled trial to determine the effect that the immersive environment has on fatigue. Participants will be randomized into 1 of 3 conditions exploring fatigue response during a typical human activity (grocery shopping). The level of cognitive and emotional challenges will change during each activity. The primary outcome of phase 1 is the experience of user interface difficulties. The primary outcome of phase 2 is self-reported CF. The core secondary phase 2 outcomes include subjective cognitive load, change in task performance behavior, and eye tracking. Phase 2 uses within-subject repeated measures analysis of variance to compare pre- and postfatigue measures under 3 conditions (control, cognitive challenge, and emotional challenge).

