### Strengths and Limitations of This Study

CF is a complex phenomenon influenced by task, environment, personal experience, and individual differences. Our experimental conditions included a familiar task performed in a realistic immersive VR environment that allows for the precise control of stimuli. The ability to control stimuli and timing of events will enable us to determine the relative contribution of distraction, boredom, task complexity, and person characteristics on the development of CF. The strength of the immersive VR experience is the capacity to create a cognitive experience that closely aligns with real-life demands. Our ability to control the presence and timing of interfering factors enables us to assess environmental influences that would be almost impossible to standardize using an actual grocery store.

The immersive VR environment allows us to seamlessly use multiple measures of CF. We will use subjective indicators of CF and workload to better understand how perceived fatigue (eg, physical fatigue: *tiredness* and *sleepiness;* cognitive fatigue: *efficiency* and *difficulty in concentrating*) and workload (eg, mental demand, effort, and frustration) relate to the effects of tasks, environments, and other factors. Potential objective measures of CF, such as changes in behavior (eg, performance efficiency, shopping list rechecking, rate, and the efficiency of movement) and changes in eye movement, can be measured unobtrusively. The use of a randomized controlled design is a strength of this study. Participants will be randomly assigned to 1 of the 3 shopping conditions to control for any confounding effects of person-level background characteristics (eg, age) that may affect fatigue or reactions to the VR experience.

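### Workload is a secondary outcome in the abstract and objectives, but the phase 2 analysis section writes it into the primary hypothesis; the primary comparisons differ as well

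*Protocol article*

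**What the plan says.** Abstract, Methods: "The primary outcome of phase 2 is self-reported CF". The next sentence reads "The core secondary phase 2 outcomes include subjective cognitive load, change in task performance behavior, and eye tracking".

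Introduction, Objectives: "The primary outcome measure in phase 2 is the self-reported change by participants in CF by shopping experience". The primary hypothesis there has two parts, both about fatigue. The first is that "individuals performing structured grocery tasks will report more CF than simple exploratory behavior in the grocery store". The second is that people who meet distractions and interruptions report more fatigue than people who do not. Workload appears later, at a lower level: "Specific secondary exploratory hypotheses include that perceived workload increases with time on task".

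Methods, Analysis, Phase 2, first paragraph: the lead repeated measures ANOVA takes VAS-F and NASA-TLX together as dependent variables by shopping experience. The secondary analyses that follow cover objective indicators only (eye tracking, shopping performance, cognitive functioning). NASA-TLX is not among them.

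Same section, second paragraph, on the purpose of the ANOVA: "test the primary hypothesis that the cognitive activity of shopping for specific items will create a greater perception of mental workload and fatigue". The comparator there is only exploring the store. Interruptions are not mentioned in that sentence.

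**The concern.** One outcome cannot be secondary in the abstract and part of the primary hypothesis in the analysis. The article itself treats the two constructs as different: the Fatigue Assessment section describes workload as closely linked to CF and names NASA-TLX as a workload measure.

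The difference affects what the trial may conclude. The control experience has no task to complete, while experience 2 has a shopping list and experience 3 adds frustrating events. The workload ratings cover mental demand, effort and frustration. These ratings could plausibly separate the arms whether or not CF does. Under the analysis section's wording, that result could be presented as support for the primary hypothesis. Under the abstract and the Objectives it could not.

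The comparisons diverge too. The Objectives make interruptions versus none part of the primary hypothesis. The analysis sentence that carries the primary label names only shopping versus exploring. While both versions stand, the choice between them could be made after the results are seen.

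**Working it through.** **Roles side by side**

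| Place | CF / VAS-F | Workload / NASA-TLX | Primary comparisons |
|---|---|---|---|
| Abstract, Methods | primary | core secondary | not itemised |
| Objectives | primary | secondary, exploratory | structured vs exploration; interruptions vs none |
| Analysis, Phase 2, paragraph 1 | lead ANOVA | lead ANOVA, not listed under secondary analyses | by shopping experience, with interruptions mentioned |
| Analysis, Phase 2, paragraph 2 | in the primary hypothesis | in the primary hypothesis | shopping vs exploring only |

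The only effect size quoted for the sample size of 60 (Participants section) is for VAS-F, Cohen d = 0.65. Vigilance decrement studies are also cited. No NASA-TLX effect is given, which fits CF as the single primary outcome.

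**What the ambiguity is worth**

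The article states no significance level and no error rate, so there is no figure of its own to reproduce. Assumptions: 5% two-sided per test, 20 per arm (60 over three arms; the phase 2 allocation ratio is not stated), and no true effect on either outcome.

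- VAS-F alone on one comparison: 5%.
- Either outcome may count, one comparison: P(either) = 0.05 + 0.05 − P(both). If the outcomes are independent this is 1 − 0.95² = 0.0975. With correlated outcomes it was simulated (40,000 null trials, two-sample t tests).
- Both outcomes required: simulated with the three-arm ANOVA test for each outcome.

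| Correlation of the two outcomes | Either counts, one comparison | Both required, ANOVA |
|---|---|---|
| 0 | 10.0% | 0.3% |
| 0.3 | 9.4% | 0.4% |
| 0.5 | 9.1% | 0.8% |
| 0.7 | 8.4% | 1.5% |
| 0.9 | 7.3% | 2.8% |

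So the same text allows a false primary success rate of about 7% to 10% on one reading, and below 5% on the other.

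These figures describe the case of no effect on either outcome. If workload truly differs and CF does not, the chance of a primary claim based on workload is the power of the NASA-TLX test. The article gives no effect size from which to compute it.

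**The case against.** The wording joins workload and fatigue with *and*. Read literally, both must be shown. That gives no inflation, only a stricter primary hypothesis. This stands, and it is why the 7% to 10% is conditional. It does not remove the conflict, because a joint requirement also differs from the CF-only primary in the abstract and the Objectives.

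A true workload difference is not a false positive. This stands too. The main harm is mislabelling: a secondary finding reported as primary.

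The workload hypothesis in the Objectives concerns increase with time on task, not the difference between conditions. It is therefore weaker support than the abstract, which classifies workload directly. The analysis sentence also opens as an example, so its silence on interruptions may be incomplete rather than deliberate. That softens the point about comparisons, but the sentence still attaches the primary label to workload.

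Three stronger readings are tempting and are not supported:

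- A reader might multiply two outcomes by two comparisons and infer a four-test primary family with a much larger error rate. No section states that family: the second comparison comes from the Objectives, where it concerns fatigue only. Two VAS-F comparisons alone would already give about 9% if either counted, so the larger rate could not be put down to workload. A multiplicity rule may also stand in a fuller document.
- A reader might infer that the whole VAS-F, physical items included, is the analysed score. The article says only that an adapted version is used and does not describe scoring. The Strengths and Limitations section separates physical from cognitive fatigue, which is compatible with separate scores.
- A reader might conclude that the two comparisons must be tested in a fixed order. That is one option with a real price. At d = 0.65 between arms and 20 per arm, the first comparison would have about 52% to 54% power, so the second would often go untested.

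**Conclusion.** The contradiction is explicit in the current text and does not depend on any document not shown. Workload is secondary in the abstract and Objectives and primary in the analysis section, and the primary comparisons do not match either. The consequence is that a workload result without a CF result could be labelled primary.

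In numbers, the false-success rate for one comparison is about 7% to 10% instead of 5% if either outcome may count. This assumes 5% per test and an outcome correlation between 0.9 and 0. If both outcomes are required there is no inflation. The finding rests on the inconsistent role of NASA-TLX, not on the absence of an adjustment. It should be fixed before the data are analysed, but it does not call the design into question.

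**What to change.** - Analysis, Phase 2, second paragraph: take mental workload out of the primary hypothesis, so that it concerns fatigue only.
- Same section, first paragraph: name change in VAS-F as the sole primary dependent variable and move NASA-TLX to the secondary analyses.
- State the same primary comparisons in the Objectives and the analysis section. Either both include interruptions versus none, or neither does.

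These are changes of wording: no measure, visit or participant is added. The cost is that a workload difference on its own can no longer be claimed as a primary result. It can still be reported as secondary.

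If the sponsor does want workload as primary, the abstract and Objectives must say so, with a rule for whether one or both outcomes must succeed. Splitting 5% equally between the two outcomes would lower between-arm power at d = 0.65 and 20 per arm from about 52% to 54% to about 40% to 43%.
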